## Abstract

**Background:**

Support programs for partners of patients with acquired brain injury are necessary since these partners experience several unfavorable consequences of caregiving, such as a high burden, emotional distress, and poor quality of life. Evidence-based support strategies that can be included in these support programs are psychoeducation, skill building, problem solving, and improving feelings of mastery. A promising approach would seem to be to combine web-based support with face-to-face consultations, creating a blended care intervention.

**Objective:**

This paper outlines the protocol of a randomized controlled trial to evaluate the CARE4Carer blended care intervention for partners of patients with acquired brain injury.

**Methods:**

A multicenter two-arm randomized controlled trial will be conducted. A total of 120 partners of patients with acquired brain injury will be recruited from five rehabilitation centers in the Netherlands. The blended care intervention consists of a nine-session web-based support program and two face-to-face consultations with a social worker. Themes that will be addressed are: giving partners insight into their own situation, including possible pitfalls and strengths, learning how to cope with the situation, getting a grip on thoughts and feelings, finding a better balance in the care for the patient with acquired brain injury, thinking about other possible care options, taking care of oneself, and communication. The intervention lasts 20 weeks and the control group will receive usual care. The outcome measures will be assessed at baseline and at 24- and 40-week follow-up. The primary outcome is caregiver mastery. Secondary outcome measures are strain, burden, family functioning, emotional functioning, coping, quality of life, participation, and social network.

**Results:**

The effect of the intervention on the primary and secondary outcome measures will be determined. Additional a process evaluation will be conducted.

**Conclusions:**

The findings of this study will be used to improve the care for partners of patients with acquired brain injury. Barriers and facilitators that emerge from the process evaluation will be used in the nationwide implementation of the intervention.

**Trial Registration:**

Dutch Trial Register NTR6197; http://www.trialregister.nl/trialreg/admin/rctview.asp?TC=6197 (Archived by WebCite at http://www.webcitation.org/6xHBAxx0y)

## Introduction

Caregivers of patients with acquired brain injury (ABI), such as stroke and traumatic brain injury, often experience high levels of burden, which profoundly affects their physical and psychosocial well-being [1-5]. About half of the caregivers experience anxiety and emotional distress, and 65% report health problems and a decline in social life with high levels of strain [6]. The majority of caregivers of patients with ABI reporting psychological distress are the partners of the patients [7]. Among partners of patients who were admitted for inpatient rehabilitation, 80% reported poor quality of life one year after stroke [3]. It is especially the return home after inpatient rehabilitation which appears to be a major hurdle for patients and their caregivers [6].

Support programs for partners of patients with ABI are necessary and should be initiated as early as possible after discharge from the rehabilitation facility so partners are better prepared for their new role as caregivers at home [8]. Several reviews show that evidence-based support strategies such as psychoeducation, problem-solving therapy and skill building are effective components of interventions [9-13]. Additionally, support programs should address condition-specific issues, such as the cognitive, emotional, and personality changes of the patient [1]. Furthermore, interventions to increase feelings of mastery also seem important, since mastery can protect against the stressors of caregiving and improve caregivers’ well-being [14,15].

Participating in a support program can be challenging for partners of patients with ABI, since being a caregiver already takes up much time and energy [16], in addition to everyday activities such as having a job. Travelling to a rehabilitation center to attend a support program can be experienced as requiring too much time and energy. Web-based interventions may therefore be more suitable, since partners can participate at any time from any location with internet access, and they can keep their own pace [17]. Caregivers in various populations have reported being satisfied and comfortable with web-based interventions [18]. Previous research has shown that web-based interventions can improve family functioning, psychological well-being, coping, and quality of life among caregivers [18,19]. Furthermore, web-based interventions for caregivers are feasible [19] and can save costs [18]. A disadvantage of web-based interventions, however, is that of the higher drop-out rates [20]. Participants of web-based interventions report that adherence can be increased by combining web-based interventions with face-to-face consultations, creating a blended care intervention [21,22]. Another advantage of combining web-based interventions with face-to-face consultations is the opportunity for personalized treatment, elaborating on specific personal problems which cannot be addressed through predefined responses but require input from professional caregivers [22].

This study aims to evaluate the effects and process of a blended care intervention, which includes psychoeducation, skill building and problem solving, on feelings of mastery in partners of patients with ABI. Our hypothesis is that the intervention group will have increased feelings of mastery compared to the control group. This paper describes the study protocol.

## Methods

### Design

This study is a multicenter two-arm randomized controlled trial investigating the CARE4Carer blended care intervention in addition to usual care, in comparison to usual care alone. The Medical Research Ethics Committee of the UMC Utrecht confirmed that the Dutch Medical Research Involving Human Subjects Act (WMO) does not apply to this study. The Dutch Agreement on Medical Treatment Act (WGBO) and Dutch Personal Data Protection Act (Wbp) do apply. All participating rehabilitation centers have approved the study protocol. Written informed consent is obtained from each participant. The study is registered in the Dutch trial register as NTR6197, registered 2 November 2016.

### Participants

The study population consists of partners of patients with ABIs such as stroke, subarachnoid hemorrhage, traumatic brain injury, postanoxic encephalopathy (ie, acute onset, no degenerative neurological diseases). Participants are recruited from five rehabilitation centers in the Netherlands (Adelante, Heliomare, Reade, Sint Maartenskliniek, Tolbrug). Inclusion criteria for both patient and partner are: (1) 18 years or older, and (2) written informed consent. Additional inclusion criteria for the patient are: (1) having an ABI, (2) independent living in the community before the ABI, (3) having been admitted for inpatient rehabilitation, and (4) being scheduled to be discharged home after rehabilitation. Additional inclusion criteria for the partner are: (1) being one of the patient’s primary caregivers, and (2) being the patient’s partner. Exclusion criteria for the patient are: (1) neurodegenerative or progressive ABI and (2) insufficient command of Dutch, clinically judged by the health care professionals. Exclusion criteria for the partner are: (1) insufficient command of Dutch, clinically judged by the health care professionals, (2) being unable to work on a computer, and (3) having no internet access. Partners can only participate when the patient signs informed consent. If the patient decides to stop study participation, the partner can continue to participate, but data of the patient will not be used in the analyses.

### Procedure

The participants are recruited during regular consultations with a social worker during inpatient rehabilitation. The social workers, who are trained in the treatment protocol, check the eligibility criteria and explain the study. Both partner and patient receive an information letter and an informed consent form and are asked whether the researcher may contact them. After a few days, the researcher calls the partner and asks if there are any questions about the study. When both partner and patient agree to participate, they sign their informed consent forms and return these to the researcher by mail. Reasons for exclusion and reasons to decline research participation are recorded. Randomization takes place after the informed consent forms have been received.

Demographic factors of the partners are recorded at baseline and those of the patients are retrieved from the patient records. The outcome measures for the partners are assessed at baseline, postintervention and at follow-up, except for care consumption, which is not assessed at baseline. The outcome measures for the patients are assessed at baseline and at follow-up. Questions regarding process evaluation are presented after the intervention. All questionnaires are administered through the same platform, which also provides the web-based support program. See Figure 1 for the flow diagram.

### Randomization

Participants are randomly assigned to either the group receiving the CARE4Carer intervention or to the usual care control group, using an online randomization tool **.** Participants are stratified by rehabilitation center, and block randomization with two block sizes (2 and 4) is used to achieve a balance across the experimental and control groups. The block size and order of allocation are randomly chosen at the beginning of each block. This minimizes the risk of predicting group assignment and keeps the researcher blinded to the randomization process. Randomization takes place before the baseline measurement to be able to assign a certain route to the partner in the online platform. Partners in the intervention group automatically gain access to the web-based support program directly after completing the baseline measurement, which is only possible when this route is set beforehand.

### CARE4Carer Intervention

The CARE4Carer intervention starts two weeks after the patient is discharged from inpatient rehabilitation and consists of a web-based support program and face-to-face consultations with a social worker.

### Web-Based Support Program

The intervention program, called Brain injury – Moving forward together (in Dutch: “Hersenletsel – hoe samen verder?”), is a web-based support program for partners of patients with ABI. The program comprises 9 sessions, described in Textbox 1. It is based on an existing support program, which was developed by Minddistrict and Heliomare Rehabilitation Centre. They used principles of cognitive behavior theory [23] and solution-focused therapy [24], as well as expert input from social workers, psychologists, and caregivers of patients with ABI.

**Figure 1 figure1:**
[figure not shown]
Flow diagram of the trial.

We have modified this program to tailor it specific to partners of patients with ABI. We have also carried out a pilot study in which three partners of patients with ABI and a member of the patient association tested and evaluated the program. This has led to several further adaptations. Themes within the program are: getting insight into one’s own situation, including possible pitfalls and strengths, learning how to cope with the situation, getting a grip on thoughts and feelings, finding a better balance in the care for the patient with ABI, thinking about other possible care options, taking care of oneself, and communication. Each session is informative and easy to use and provides practical tips. The sessions consist of psychoeducation and assignments aimed at problem solving and skill building. Short videos featuring a social worker and videos of partners who are caregivers of patients with ABI are included in each session.

The partners can attend the program over a period of 20 weeks in their own time, at their own pace, and from any location with internet access. Partners are encouraged by automatic email reminders and by the social workers to complete the sessions before the postintervention measurement, although the program is still available for them after this period.

### Face-to-Face Consultations

In addition to the web-based support program, partners are offered two consultations with a social worker at the rehabilitation center. The social workers prepare for the meetings by reviewing the completed assignments presented in the web-based sessions. Issues emerging from these answers are addressed and specific personal situations are discussed. The first consultation takes place 10 weeks after discharged, after the first 4 sessions of the web-based program have been completed; the second consultation is after the 9^th^ session, 20 weeks after discharge. The duration of the consultations is about 45 minutes to one hour, depending on the need to elaborate.

### Usual Care

Partners randomized to the control group receive usual care. This can consist of consultations with a social worker and/or psychologist and peer support groups. Partners in the intervention group are also allowed to receive usual care in addition to the CARE4Carer intervention.

### Measures

The primary outcome is caregiver mastery. Secondary outcome measures for the partners are strain, burden, family functioning, emotional functioning, coping, care-related quality of life, participation, social network and care consumption. Secondary outcome measures for the patients are family functioning, emotional functioning, and participation. Additionally, a process evaluation will be conducted. An overview of all instruments and the time of assessment is presented in Table 1.

### Caregiver Mastery

Caregiver mastery is measured by the Caregiver Mastery Scale (CMS) [25]. This instrument is an adaptation of the Pearlin Mastery Scale [26], in order to measure mastery in the caregiving situation instead of global mastery. This questionnaire consists of seven statements about caregiving, such as “You believe you are mastering most of the challenges in caregiving.” Partners are asked to indicate their level of agreement (ie, strongly disagree, disagree, neither agree nor disagree, agree, strongly agree) with each statement. Three items with negative statements are reverse-scored. Total scores can range from 7 to 35, with higher scores reflecting greater caregiver mastery. Psychometric quality has been confirmed [25] and the instrument has proved to be able to detect change after intervention [27].

### Secondary Outcome Measures

#### Caregiver Strain Index (CSI)

The amount of strain experienced by the partner is assessed with the CSI. This instrument contains 13 statements which are scored a 1 (“yes”) or 0 (“no”) [28]. Total scores range from 0 to 13, with higher scores indicating higher strain. Scores of 7 or higher indicate substantial strain. The CSI is a reliable [28] and valid [29] instrument which is commonly used for caregivers of stroke patients [30].

#### Self-Rated Burden (SRB)

A single question enables the partners to indicate how burdensome caring for the patient with ABI is at that moment. A visual analogue scale is used, ranging from 0 (“not hard at all”) to 100 (“much too hard”) [29]. The SRB has proved to be a valid instrument to assess the burden of caregiving for informal caregivers of patients with stroke [29].

Sessions of the CARE4Carer web-based intervention.WelcomeCaring for your partnerBurden and resilienceWhich care choices to make?Getting a grip on your thoughts and feelingsTaking care of yourselfAsking for supportCommunicationAnd now?

**Table 1 table1:** Overview of all instruments.

Instruments	T0		T1		T2	
	C **^a^**	P **^b^**	C	P	C	P
Caregiver Mastery Scale	x		x		x	
Caregiver Strain Index	x		x		x	
Self-Rated Burden	x		x		x	
McMaster Family Assessment Device Subscale: General Functioning	x	x	x		x	x
Hospital Anxiety and Depression Scale	x	x	x		x	x
Utrecht Coping List	x		x		x	
CarerQol	x		x		x	
Utrecht Scale for Evaluation of Rehabilitation – Participation Subscale: Restrictions	x	x	x		x	x
Social network	x		x		x	
Care consumption			x		x	
Process evaluation			x			

^a^C=caregiving partner.

^b^P=patient.

#### McMaster Family Assessment Device (FAD)

Family functioning is assessed with the General Functioning subscale of the FAD [31]. Partners indicate their level of agreement (ie, strongly disagree, disagree, agree, strongly agree) with 12 statements. Each statement is scored from 1 to 4, with 1 reflecting healthy functioning and 4 reflecting unhealthy functioning. A mean score of 2.0 or higher indicates problematic family functioning [32]. The FAD has good psychometric properties [31-33].

#### Hospital Anxiety and Depression Scale (HADS)

Emotional functioning is measured with the HADS. It consists of two 7-item subscales measuring anxiety and depression. Scores above 7 on the subscales indicate an anxiety disorder or depression, respectively [34]. The HADS has good psychometric properties and has proved to be responsive to change [35,36].

#### Utrecht Coping List (UCL)

Coping is assessed with three subscales of the Utrecht Coping List: (1) active problem solving (7 items), (2) seeking social support (6 items), and (3) passive reacting (7 items) [37]. A 4-point rating scale is used, ranging from “seldom or never” to “very often”. Higher scores on a subscale indicate a greater tendency to use that specific coping style. The UCL has good psychometric properties [37,38].

#### CarerQol

The CarerQoL instrument measures the care-related quality of life of informal caregivers [39]. It determines the subjective burden in seven dimensions of the caregiving situation (CarerQol-7D) and includes a valuation component (CarerQol-VAS). Low scores on the CarerQol-7D indicate a poor caregiving situation, while high scores on the CarerQol-VAS reflect a higher level of happiness. The CarerQol is a valid tool to measure the impact of caregiving [40].

#### Utrecht Scale for Evaluation of Rehabilitation – Participation (USER-P)

Participation restrictions are assessed with the USER-P instrument [41]. On 10 items, respondents indicate to what extent they are able to do the activity described. Scores range from 0 (“not possible”) to 3 (“without difficulty”). Higher total scores indicate fewer participation restrictions. The USER-P has good psychometric properties [42,43].

#### Social network

The social network (ie, number of parents/step-parents, children/grandchildren, other family members, and friends/neighbors) is mapped using a newly developed questionnaire. It also includes items about how easy it is to get practical and emotional help from these persons. Partners answer on a 5-point scale ranging from "very easy" to "very difficult".

#### Care consumption

Care consumption is assessed during the post-intervention (T1) and follow-up (T2) measurements. Partners are asked whether and how often they have had contact with a psychologist, social worker, general practitioner, practice nurse and/or aftercare nurse, and whether they participated in peer support groups.

### Process Evaluation

At postintervention (T1), the partners evaluate the intervention, the individual sessions, and the different elements of the intervention by filling in the online questionnaire. The advantages, disadvantages, satisfaction, and usability of the intervention are investigated.

Using interviews, we assess the experiences of the social workers with carrying out the intervention and working with a blended care program, as well as their views on facilitators and barriers for implementation. Every social worker who supported a caregiver in the intervention group will be interviewed.

Treatment fidelity is determined by reports from the social workers on the number of face-to-face consultations that have taken place and by analyzing how many sessions of the web-based support program have been completed. Partners are obliged to fill in certain assignments to be able to complete a session.

### Blinding

The baseline measurements (T0) are self-reported by partner and patient, who do not yet know the allocation outcome at this stage. Blinding to treatment allocation is not possible due to the nature of the intervention. The postintervention (T1) and follow-up (T2) measurements are, therefore, not blinded since these are self-reported by the partner and patient who are aware of treatment allocation by that time.

### Power Analysis

The sample size has been calculated on the basis of the primary outcome measure, the Caregiver Mastery Scale. To detect a difference between the groups of 0.5 SD on the Caregiver Mastery Scale, with an alpha of 0.05 and a power of 80%, a total of 50 caregivers is needed in each arm of the trial. Assuming a drop-out rate of 20%, a total of 120 patient-partner couples will be included in the CARE4Carer trial.

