### Statistical Analyses

Descriptive statistics including frequencies, means, standard deviations, and (for nonparametric data) medians and interquartile ranges will be calculated. Longitudinal data analysis will be performed using a generalized linear mixed model (GLMM), to evaluate differences in efficacy between the experimental and control groups. Data will be analyzed based on an “intention-to-treat” analysis and with an alpha level of 0.05. The analysis software IBM SPSS Statistics version 22 for Windows will be used [44]. Descriptive statistics will be used for the partners’ process evaluation and for the treatment fidelity. The interviews with the social workers will be transcribed verbatim and qualitative analyses will be performed.

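### Fifty caregivers per arm does not give 80% power for 0.5 SD at the usual two-sided 0.05 on the inputs stated; an unadjusted comparison of that size has about 70%

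*Protocol article*

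**What the plan says.** The Power Analysis section names the outcome used for sizing ("The sample size has been calculated on the basis of the primary outcome measure, the Caregiver Mastery Scale") and the target effect ("To detect a difference between the groups of 0.5 SD on the Caregiver Mastery Scale"). It then gives the error rates and the result: "with an alpha of 0.05 and a power of 80%, a total of 50 caregivers is needed in each arm of the trial". A 20% drop-out allowance takes the total to 120 couples.

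The Statistical Analyses section plans a longitudinal generalized linear mixed model on an intention-to-treat basis, "and with an alpha level of 0.05". Neither section says whether 0.05 is one-sided or two-sided. Neither mentions a correlation between repeated mastery scores or an adjustment for baseline. The Introduction words the hypothesis directionally: "Our hypothesis is that the intervention group will have increased feelings of mastery compared to the control group".

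**The concern.** The section prints every input of a standard two-group sample size calculation, together with the answer. An alpha of 0.05 with no qualifier is ordinarily taken as two-sided, and on that reading the answer does not follow from the inputs: 50 is 13 to 14 per arm too few. Something that would justify 50 has been left unsaid.

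This is the only sample size justification for the primary outcome. A reader who takes it at face value believes that a true 0.5 SD benefit would be missed one time in five. For an unadjusted two-sided comparison the risk is about three in ten, so a null result would seem to count against a 0.5 SD effect more strongly than it should. The Discussion makes nationwide availability depend on the intervention proving superior to usual care, so a missed effect has a practical consequence.

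**Working it through.** **Inputs from the Power Analysis section.** Difference d = 0.5 SD; alpha 0.05, sidedness not given; power 80%; 50 per arm; drop-out 20%; total 120. Equal allocation is inferred from the equal arm sizes and the balanced blocks in the Randomization section.

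**Formula (two independent means, normal approximation).** n per arm = 2 × (z_alpha + z_beta)² / d², with z_beta = 0.8416 for 80% power.

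**Step 1: reproduce the stated 50.** With one-sided 0.05, z_alpha = 1.6449:

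2 × (1.6449 + 0.8416)² / 0.25 = 49.5, so 50 per arm.

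The t-test version gives 50.15, and power at 50 per arm is 79.9%. The stated figure is reproduced.

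**Step 2: the usual two-sided 0.05.** With z_alpha = 1.9600:

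2 × (1.9600 + 0.8416)² / 0.25 = 62.8, so 63 per arm. The t-test version gives 63.8, so 64.

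**Step 3: two-sided power for 0.5 SD, unadjusted.**

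| Evaluable per arm | Where it comes from | Normal approximation | t-test |
|---|---|---|---|
| 48 | 120 × 0.80 = 96, halved | 68.8% | 67.9% |
| 50 | stated requirement | 70.5% | 69.7% |
| 60 | 120 with no drop-out | 78.2% | 77.5% |

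Even with every couple retained, the unadjusted two-sided comparison stays below 80%.

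**Step 4: effect detectable with 80% power, two-sided, t-test.** 0.566 SD at 50 per arm and 0.578 SD at 48 per arm.

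**Step 5: could baseline adjustment explain 50?** Adjusting for a baseline score that correlates r with follow-up multiplies the outcome variance by (1 − r²). The standardized effect becomes 0.5 / √(1 − r²), which must equal the detectable effect from Step 4:

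- 50 per arm: r = √(1 − (0.5/0.566)²) ≈ 0.47
- 48 per arm: r = √(1 − (0.5/0.578)²) ≈ 0.50

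The normal approximation gives about 0.45 at 50 per arm, since 62.8 × (1 − 0.45²) ≈ 50. A two-sided calculation can therefore also arrive at 50, but only with a correlation that the article does not state.

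**The case against.** **The article never says two-sided, so 50 is not a miscalculation.** This stands as far as it goes. With one-sided 0.05 the arithmetic is right, and the hypothesis is directional. But a directional expectation does not specify a test, and a one-sided 0.05 test departs from the usual reading and has to be declared. If it was intended, the section omits the assumption that produces its number.

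**The origin of 50 is unknown.** This stands. A reader might conclude that a one-sided formula was certainly used. No formula is given, and Step 5 shows another route to the same number. The one-sided origin is an inference. The shortfall for an unadjusted two-sided test does not depend on it.

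**The 70% belongs to a test that is not planned.** This also stands, and it limits the conclusion. Mastery is measured at baseline and twice afterwards, and a longitudinal mixed model is planned. As an illustration, take two-sided tests, 50 per arm, the same correlation r between any two visits and a constant 0.5 SD effect:

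| r | Baseline-adjusted, one visit | Change score, one visit |
|---|---|---|
| 0.3 | about 74% | about 55% |
| 0.5 | about 82% | about 70% |
| 0.7 | about 93% | about 89% |

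A baseline-adjusted average of both follow-ups would reach about 91% or more over this range. Power in the actual analysis may lie well above or below 70%, so it would be wrong to infer that the trial will have 70%. The model may also use partners who give only one follow-up, so 48 per arm treats drop-outs as contributing nothing. Still, the printed justification relies on none of this.

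**An article condenses, and the detail may sit elsewhere.** That would answer a complaint about missing detail. Here the printed inputs and the printed answer disagree on their ordinary reading, and a fuller document does not change what is printed.

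**Conclusion.** The point holds in a limited form. On the inputs given, with alpha read as two-sided and an unadjusted comparison at one time point, 80% power for 0.5 SD needs 63 to 64 per arm. Fifty per arm gives about 70%, a type II error of about 30% rather than 20%, and reaches 80% only for 0.57 SD. The 48 per arm left after 20% loss from 120 gives about 68%.

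The 80% claim needs either a one-sided test or a baseline correlation near 0.47, and the article states neither. The documents do not support saying that the arithmetic is wrong in itself, that a one-sided formula was definitely used, or that the planned mixed model will have only 70% power. Naming SPSS as the software does not settle the sidedness either.

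**What to change.** Keep 120 couples and revise the Power Analysis section.

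1. State that the primary test is two-sided at 0.05.
2. Then do one of the following:
   - Restate the power: for an unadjusted comparison with 50 evaluable caregivers per arm, about 70% for 0.5 SD, and 80% for 0.57 SD.
   - Keep 80%, but base it explicitly on a baseline-adjusted primary analysis and give the correlation assumed between baseline and the 24-week score: about 0.47 with 50 evaluable per arm, or 0.50 with 48. That correlation can be checked on pooled data without unblinding.

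The second option fits the longitudinal analysis better, provided that the primary analysis does adjust for baseline.

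The cost is wording only, with no extra participants; recruitment was still under way when the article was written. The downside is that the stated power becomes less favourable, or conditional on a correlation that may turn out lower than assumed.

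### Enrolling 120 couples with 20% drop-out leaves 96 partners (48 per arm), 4 short of the 100 that the power analysis requires

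*Protocol article*

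**What the plan says.** The Power Analysis section bases the sample size on the Caregiver Mastery Scale. The target is set as "To detect a difference between the groups of 0.5 SD on the Caregiver Mastery Scale", with alpha 0.05 and power 80%, and the result is that "a total of 50 caregivers is needed in each arm of the trial". The next sentence moves from the required number to the enrolled number: "Assuming a drop-out rate of 20%, a total of 120 patient-partner couples will be included in the CARE4Carer trial".

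The Methods paragraph of the abstract repeats the total ("A total of 120 partners of patients with acquired brain injury will be recruited") but gives neither a drop-out rate nor a required number. It carries the figure forward and is not a second calculation. Nothing else in the article defines the drop-out rate differently or gives another reason for 120.

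**The concern.** Three figures stand in two adjacent sentences: 100 partners needed, 20% lost, 120 enrolled. A drop-out rate is ordinarily a share of those enrolled, and on that reading the three cannot all be true. If drop-out is exactly as assumed, the trial ends with fewer partners than its own calculation asks for.

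What is at stake is the accuracy of the stated allowance. A reader will take it that the trial keeps its planned number with up to one in five partners lost, and it does not. The Introduction itself notes that drop-out tends to be higher in web-based interventions, so the tolerance deserves to be stated correctly.

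**Working it through.** **Inputs.** From Power Analysis: difference 0.5 SD, alpha 0.05, power 80%, 50 per arm, drop-out 20%, enrolment 120. Allocation is taken as 1:1, from the equal numbers per arm and from Randomization ("block randomization with two block sizes (2 and 4) is used to achieve a balance across the experimental and control groups"). Sidedness is not stated. The hypothesis in the Introduction is directional ("Our hypothesis is that the intervention group will have increased feelings of mastery compared to the control group"), so both cases are computed.

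**Step 1: reproduce 50 per arm.** The formula is n per arm = 2(z_alpha + z_power)² / d², with d = 0.5 and z_power = 0.842.
- One-sided: 2 × (1.645 + 0.842)² / 0.25 = 49.5, rounded up to 50. The t-test version gives 50.2. This matches the plan.
- Two-sided: 2 × (1.960 + 0.842)² / 0.25 = 62.8, rounded up to 63. The t-test version gives 63.8. This does not match.

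**Step 2: reproduce 120.** The requirement is 2 × 50 = 100.
- 100 × (1 + 0.20) = 120. This matches the plan exactly.
- 100 / (1 − 0.20) = 125. This does not match. Worked by arm, 50 / 0.8 = 62.5, rounded up to 63, or 126 in total with equal arms.

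**Step 3: what 120 delivers.**
- Remaining after 20% loss: 120 × 0.80 = 96, or 48 per arm.
- Shortfall: 100 − 96 = 4.
- Largest drop-out rate that still leaves 100: 1 − 100/120 = 16.7%.

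**Step 4: effect on power.** This is a two-sample comparison at d = 0.5 with non-centrality 0.5 × √(n/2), which is 2.500 at n = 50 and 2.449 at n = 48.

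| Basis | 50 per arm | 48 per arm | Change (points) |
|---|---|---|---|
| One-sided, t-test | 79.9% | 78.4% | −1.5 |
| Two-sided, t-test | 69.7% | 67.9% | −1.8 |
| One-sided, normal approximation | 80.4% | 78.9% | −1.5 |
| Two-sided, normal approximation | 70.5% | 68.8% | −1.7 |

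On either basis and with either method, the loss due to the drop-out step is between 1.5 and 1.8 percentage points.

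**The case against.** The strongest reply is that this hardly matters. Four partners and less than two points of power are well inside the uncertainty of a 0.5 SD target and a 20% drop-out guess. That stands as a statement about size. It does not make the three figures agree.

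A second reply is that drop-outs are not wholly lost. Statistical Analyses plans a longitudinal mixed model by intention to treat, and Table 1 schedules the mastery scale at T0, T1 and T2, so a partner who leaves after T1 still contributes. Participants also lets a partner continue if the patient withdraws. This stands in part: the real loss of information may be smaller than the t-test figures suggest. But the Power Analysis section makes its own allowance for drop-out and so counts those partners as lost. The later choice of model does not repair that sentence.

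A third reply is that the article never says it multiplied by 1.2. That is right. The multiplication fits exactly and the division does not, but the step is not shown, so the cause is an inference. The inconsistency holds however 120 was reached.

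Condensing a protocol into an article is no answer here, because nothing is said to be missing. All three figures are printed.

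**Conclusion.** The point holds and is minor in size. Under its own 20% assumption the plan retains 96 partners against a requirement of 100, and power falls by about 1.5 points one-sided or 1.8 points two-sided. This rests on drop-out being a share of those enrolled, on 1:1 allocation, and on an unadjusted two-group comparison in which drop-outs contribute nothing. The planned mixed model may soften the loss.

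Two stronger readings are tempting and are not supported:

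- A reader might infer that this error takes power from 80% down to 67.9%. It does not. Two-sided power is already 69.7% at the stated 50 per arm with no drop-out error. The 10.3 points from 80% to 69.7% come from the unstated sidedness of the calculation, which is a separate question.
- A reader might infer that enrolment has to rise to 125 or 126. The size of the loss does not call for that. What is wrong is the statement of what 120 couples provides.

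**What to change.** Leave enrolment at 120 and correct the sentence in Power Analysis in one of two ways:

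1. State that with 120 couples a 20% drop-out leaves 96 partners, 48 per arm, and give the power for 0.5 SD at that number, saying whether the test is one-sided or two-sided (78.4% or 67.9% by t-test).
2. State that 120 couples keeps 50 per arm with drop-out of up to 16.7%.

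If the requirement of 50 per arm is itself revised once sidedness is settled, redo the drop-out step at the same time, dividing by one minus the drop-out rate.

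The cost is one sentence and a slightly less favourable figure. No procedure, analysis or participant number changes. The Results section says enrolment is ongoing, so the correction can be made before results are reported.
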